#### Estimated CO_2_ emissions

Transport-derived CO_2_ emissions will be calculated by multiplying the distance travelled by each motorized mode (determined through GPS and accelerometer data) by the mode’s average emissions factors following the procedure outlined by Neves and Brand [49]. For travel by bus, train and other non-car modes, the total distance travelled in past week, based on GPS and travel diary data, will be multiplied by the average emissions factors based on UK Green House Gases reporting guidelines [50]. For cars, CO_2_ emissions will be estimated by considering the car size (based on engine size), fuel type, vehicle age, number of cold starts (calculated as the number of reported trips) and average speed (using GPS data). These factors underlie the National Atmospheric Emissions Inventory and will be obtained from DEFRA [50].

#### E-cycling during the intervention

The number of e-cycling journeys, the distance travelled on the e-bike and the pattern of e-bike use throughout the 12-week intervention will be determined through use of a cycling GPS unit (Garmin Edge 130). The GPS device will attach directly to the bicycle. Data will be automatically uploaded to the Garmin Connect website via Bluetooth connection with the participant’s phone or manually by the instructor at monthly intervals during meeting times (if the participant does not wish to track their e-cycling via the Garmin Connect website). Participants will be provided with instructions on how to use the device and a power cable to charge the device. The e-bike odometer, which is permanently attached to the bike, will provide a total measure of total distance travelled over the three-months.

### Analysis plan

#### Quantitative analysis

The primary outcomes of this pilot trial include recruitment and consent rates, retention and adherence to study procedures and data provision. Analysis of these data will be descriptive, expressed as frequencies and percentages. Any adverse events will be described appropriately. Characteristics of the sample will be summarized using descriptive statistics (means and standard deviations, medians and interquartile ranges, or frequencies and percentages as appropriate). Descriptive comparisons of these data will be made between the intervention and the waitlist control. Evidence of promise of the intervention (i.e., whether the intervention can lead to changes in outcomes measures) will be examined using comparison of change scores between conditions for all outcome measures (except e-cycling during the intervention). See Table 2 for a description of the outcome measures and proposed analysis plan for each outcome. Effect estimates will be presented with 95% confidence intervals reported; *p* values will not be considered as the study is not powered to detect effectiveness.

**Table 2 Tab2:** List of PEDAL-2 study objectives, associated outcomes, data collection tools, time point measurements and analysis plan

Study objectives	Outcome	Data collection method/tool	Time point of measurement			Analysis plan
			Baseline (T0)	During intervention	Follow-up (T1)	
1. Identify effective methods of recruiting individuals with T2DM	• # GP practices approached; # that agree to act as PIC • # individuals identified through GP database searches; response rate to information letters • # participants recruited from each recruitment setting • # individuals that consent to be part of the study	Study records	X			Frequencies and percentages
2. Determine participants willingness to be randomized, study retention rates, adherence to the intervention and data collection methods and report harmful outcomes	• # participants retained in study following randomization • # Individuals that complete follow-up testing • # of participants that attend each of the intervention sessions and data collection sessions • # of harmful events	Study records		X		Frequencies and percentages
3. Assess intervention fidelity	• # of training sessions attended by participants and additional contact with instructors • Extent to which intervention content is completed as planned	Intervention checklists		X		Frequencies and Percentages
4. Estimate the potential effect of the intervention on a range of health and behaviour outcomes to inform outcome selection in future trials	• Weight, height, BMI	Tanita digital scales, SECA 700	X		X	Comparison of change scores between conditions
	• Waist circumference	Non-stretch tape measure	X		X	
	• Fasting glucose, insulin, lipids, C-reactive protein, HOMA-IR, HOMA-B	8-mL blood sample	X		X	
	• OGTT outcomes: iAUC for glucose and insulin, Matsuda index, insulinogenic index and oral glucose disposition index	2 mL blood samples at 15, 30, 45, 60, 90, 120 min post 75 g of anhydrous glucose	X		X	Reporting of effect estimates with 95% CI
	• Health-related quality of life: physical and mental summary	Short Form 36 Health Survey [39]	X		X	
	• Cardiorespiratory fitness	Maximum oxygen uptake using cycle ergometer	X		X	
	• Body composition: whole-body fat mass, regional fat mass, whole-body lean mass, regional fat mass	Dual-energy x-ray absorptiometry	X		X	Comparison of change scores between conditions
	• Femur intermuscular adipose tissue, muscle density and muscle cross-sectional area	Peripheral quantitative computer tomography				
	• Total physical activity (time spent in moderate-to-vigorous physical activity)	Actigraph (GT3X)	X		X	Reporting of effect estimates with 95% CI
	• Moderate to vigorous physical due to e-cycling and other modes of active travel	Actigraph (GT3X), Actiheart and QStarz GPS				
	• Transportation modes (walking, cycling, e-cycling, car, bus, train)	Actigraph (GT3X), Actiheart and QStarz GPS	X		X	
	• Trip purpose (e.g., commuting, business, education, escorting, shopping, visiting friends, entertainment, recreation)	Travel diary	X		X	
	• Estimated CO_2_ emissions	Actigraph (GT3X) and QStarz GPS, travel diary following procedures by Neves and Brand [48]	X		X	
	• E-cycling behaviour: # journeys, distance travelled, pattern of e-bike use	Bike odometer and Garmin 130 GPS		X		Mean and SD
Qualitatively examine the acceptability of the intervention and study procedures to participants and instructors	• Acceptability of intervention to participants • Acceptability of study procedures to participants • Acceptability of intervention delivery to instructors	Semi-structured interviews			X	Thematic analysis based on objective
Qualitatively examine participants experiences of e-cycling	• Participants barriers and facilitators to e-cycling	Semi-structured interviews			X	Thematic analysis based on objective

*T2DM* type 2 diabetes mellitus, *GP* general practitioner, *PIC* participant identification center, *HOMA-IR* Homeostasis Model Assessment for assessing insulin resistance, *HOMA-B* homeostatic model assessment for assessing β-cell function, *OGTT* oral glucose tolerance test, *iAUC* incremental area under the curve, *CO*_*2*_ carbon dioxide, *CI* confidence interval, *SD* standard deviation

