### Sample size

We aim to recruit and randomize 40 individuals for the pilot study. This sample size is based on recommendations for pilot studies which aim to provide an estimation of a standard deviation for use in the sample size calculation to inform a larger randomized controlled trial [31, 32]. There are no explicit targets regarding the number of individuals to be recruited or screened as we are investigating de novo the feasibility of recruitment from primary care. Based on recruitment rates in a similar population and region, we would anticipate a recruitment rate of approximately 30% [33]. Recruitment rates are anticipated to be slightly lower for a cycling intervention compared to a combined diet and exercise intervention, with a previous e-cycling feasibility study reporting a recruitment rate of approximately 20% [29]. Recruitment and screening will close when 20 participants have been randomized to each of the two study arms. The number of individuals invited to participate in the study and the numbers recruited will be recorded. Based on a previous feasibility study, a retention rate of approximately 80% is anticipated [29].

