### Allocation and randomization

Randomization will occur after consent is obtained and baseline (T0) data has been collected. Forty individuals will be stratified based on sex and then randomly assigned to either the e-cycling intervention or waitlist control in a 1:1 allocation ratio. Permuted blocks of random size will be used. The Biomedical Research Centre data manager will generate the random allocation sequences which will be accessible through a password protected web page. Researchers will enter the participant ID code and sex into the web page, and a random allocation will be issued. Researchers will be aware of the group allocation. Participants will be informed of the group allocation via telephone by a member of the research team. Blinding of intervention allocation will not be possible for any participant involved in the trial. A maximum of 20 participants will be randomized to each of the trial arms.

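### Between-arm effects are specified as change-score comparisons with no stated adjustment for baseline value or sex; regression on both would be more precise for continuous outcomes with low to moderate baseline-to-follow-up correlation

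*Protocol article*

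**What the plan says.** In the Analysis plan (Quantitative analysis), evidence of promise is to come from "comparison of change scores between conditions for all outcome measures (except e-cycling during the intervention"). The same paragraph adds: "Effect estimates will be presented with 95% confidence intervals reported", and that p "values will not be considered as the study is not powered to detect effectiveness". The analysis column of Table 2 carries the same instruction for the health and behaviour outcomes. E-cycling during the loan is the exception and is summarized by mean and SD.

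Under Allocation and randomization, baseline data are collected before allocation and "Forty individuals will be stratified based on sex and then randomly assigned". The arms are capped: "A maximum of 20 participants will be randomized to each of the trial arms".

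The Sample size section bases the 40 participants on "recommendations for pilot studies which aim to provide an estimation of a standard deviation for use in the sample size calculation" and expects about 80% retention. The Background gives the effect estimates one purpose, to help choose outcomes for future trials.

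No model is described, and no covariate is named in the text or in Table 2.

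**The concern.** The natural reading of the text is a difference in mean change between arms. That estimator uses the baseline value, but with a slope fixed at 1. If the baseline and follow-up SDs are equal, the regression slope of follow-up on baseline is r, which is below 1 for any outcome measured with noise or natural variation. Subtracting the whole baseline then over-corrects: the arm that happens to start higher tends to show the larger fall. With 16 to 20 per arm, such chance differences are to be expected on some of the many outcomes. Stratifying by sex does not balance each outcome's own baseline.

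At stake are the only quantitative results on promise. With no p values, the estimates and their intervals are the whole of that result, and they are meant to guide the choice of outcomes for later trials. The loss of precision also differs by outcome. It is largest where r is low, so candidate outcomes would be compared with unequal and partly avoidable noise. Outcomes taken from a single monitored week (MVPA, travel, CO2) could plausibly have lower correlations than weight or DXA measures, although the protocol gives no figures.

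**Working it through.** **The plan's own figure.** The 40 participants rest on cited recommendations, with no effect size, SD or power, so the number cannot be recomputed.

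**Inputs from the protocol.** 20 per arm and about 80% retention give 20 × 0.8 = n = 16 completers per arm, N = 32. Intervals are 95%.

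**Assumptions.** Baseline and follow-up SDs are equal and set to 1, so results are in SD units. The correlation r runs from 0.3 to 0.95. Sex is given no prognostic value.

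**Interval half-widths.**

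- Change score: t(0.975, 30) × √(2(1-r)) × √(2/16) = 0.722 × √(2(1-r)).
- Regression on arm, baseline and sex (k = 2 covariates): t(0.975, 28) × √(1-r²) × √(2/16) × √(1 + 2/27) = 0.751 × √(1-r²). The last root is √(1 + k/(N-k-3)), the expected cost of estimating the two covariate effects.

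| r (assumed) | Change score | Baseline + sex | Change-score interval relative to regression |
|---|---|---|---|
| 0.3 | 0.854 | 0.716 | 19% wider |
| 0.5 | 0.722 | 0.650 | 11% wider |
| 0.7 | 0.559 | 0.536 | 4% wider |
| 0.8 | 0.457 | 0.450 | under 2% wider |
| 0.9 | 0.323 | 0.327 | about 1% narrower |
| 0.95 | 0.228 | 0.234 | about 3% narrower |

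**Simulation check** (16 per arm, 5000 runs, sex exactly balanced within arm). The ratio of mean half-widths, regression to change score, was 0.885 at r=0.5, 0.941 at r=0.7, 0.968 at r=0.8, 0.995 at r=0.9 and 1.008 at r=0.95. These are slightly kinder to regression than the formula, which also charges for chance imbalance in sex. Both agree that the advantage has gone at about r=0.9.

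**Large-sample comparison.** The variance ratio 2/(1+r) would give change-score intervals 24%, 15%, 8% and 5% wider at r = 0.3, 0.5, 0.7 and 0.8. It leaves out the degrees of freedom and estimation cost, so it overstates the gain at this size.

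**Chance imbalance.** The SD of the baseline difference between arms is √(2/16) = 0.354 baseline SD. Given a difference D, the expected change-score contrast moves by -(1-r)D. For a one-SD chance imbalance at r=0.5 that is 0.5 × 0.354 = 0.18 SD, about a quarter of the 0.722 half-width. At r=0.8 it is 0.2 × 0.354 = 0.07 SD.

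**The case against.** The strongest reply is that the text describes no model. Regressing the change score on arm, baseline and sex is also a change-score comparison, and it gives exactly the same arm coefficient and interval as regressing the follow-up value on those terms. Covariates may be set out in an analysis plan that is not shown. A reader might therefore infer that the protocol rules out adjustment; it does not. What stands is that the only method named is the change score, in the text and again in Table 2, and nothing shown adds to it.

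Three other stronger readings also fail:

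- **That the analysis ignores baseline or is biased.** The change score subtracts the baseline. It is unbiased over randomizations, and its interval already allows for variation in baseline imbalance. The loss is in precision, and in the estimate conditional on the imbalance that occurred.
- **That every interval is needlessly wide.** At high r there is nothing to gain. For sex, stratified blocks already limit imbalance, and any gain depends on how prognostic sex is, which is not given.
- **That the definitive trial's sample size is compromised.** The Sample size section does not say that the SD of change will be the planning input. Both time points are collected, so the follow-up SD and the correlation can be had whatever estimator is used.

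It is also true that linear regression does not suit every row of Table 2. Transport modes and trip purpose are categorical. MVPA from e-cycling is presumably near zero for almost everyone before the loan, so it has little baseline to adjust for.

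**Conclusion.** The point holds in limited form. For continuous outcomes with a meaningful baseline, the stated method gives less precise estimates than baseline- and sex-adjusted regression when r is low to moderate. At 16 per arm the excess interval width runs from about 19% at r=0.3 down to 4% at r=0.7. It is negligible at r=0.8 and nil or slightly reversed at about r=0.9 and above. These figures rest on equal SDs at both times, a non-prognostic sex effect and assumed correlations.

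The consequence is modest. The estimates are secondary and descriptive. The primary outcomes are frequencies and percentages, and no progression criterion uses an effect estimate or its interval. The change is worth making because it is cheap and improves the only numbers that speak to promise. It is not a condition for the pilot to proceed.

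**What to change.** Amend the Quantitative analysis paragraph and the matching entries in Table 2 along these lines:

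> For each continuous outcome with a meaningful baseline value, the difference between arms will be estimated by linear regression of the follow-up value (T1, or the final intervention week where that is when it is measured) on arm, the baseline value of that outcome and sex, and reported as an adjusted mean difference with a 95% confidence interval. Change scores will be summarized descriptively by arm, as will transport modes, trip purpose and MVPA attributable to e-cycling. The SD at follow-up and the correlation between baseline and follow-up will be reported as inputs to the design of a definitive trial.

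No new data are needed, because baseline is collected before randomization and sex is recorded at allocation. The cost is wording and two residual degrees of freedom per outcome, which brings a slight loss of precision for very highly correlated outcomes.

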## Methods

### Study design

This pilot study is a parallel-group 2-arm, randomized waitlist-controlled trial comparing an e-cycling intervention (PEDAL-2) against a standard-care waitlist control among individuals with T2DM. A total of 40 participants will be randomized in a 1:1 allocation ratio to the two study arms. The single-centre trial will be conducted in the city of Bristol, England. Recruitment for the trial will begin in March 2019. The majority of measures will be collected at baseline (time 0 (T0)) and immediately following the intervention period (T1). In addition, data will be collected in the final week of the e-cycling intervention (physical activity and travel behaviour) and throughout the intervention (e-cycling time and distance). Figure 1 shows the study flow diagram and Additional file 1 provides the SPIRIT checklist for reporting intervention trials.

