#### E-bike loan

Participants will be loaned an e-bike for 12-weeks. Participants will be informed that the e-bike is for use by themselves and not to be lent to friends or family. During this time, participants will be instructed to use the e-bike as they desire, this means that no specific daily or weekly cycling frequency or distance targets will be imposed on participants by the researchers. Four weeks after taking the bike home, participants will attend a ‘refresher’ session with their instructor (session 3). This session will take place at a location of the participant’s choice (i.e., at their home or in the local community) and will last approximately 2 h. The content of the session will depend on the participant’s needs but will include practicing riding skills on established or new routes and a review of participants e-cycling activity as well as action planning and goal setting for future rides. At week 8, the instructor will contact the participant by telephone to discuss the participants progress, barriers to e-cycling that have arisen, and strategies used to overcome them and e-cycling goals for the upcoming month (session 4). At the end of week 12, participants will be asked to return the e-bike to Life Cycle UK headquarters or an instructor will collect the e-bike from the participant’s preferred location. Throughout the loan period, Life Cycle UK will provide a call out e-bike maintenance service. If required, participants are instructed to call the maintenance number and a Life Cycle UK mechanic will come and repair the e-bike.

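### Mean and SD, the only analysis Table 2 gives for riding over the 12-week loan, cannot show how many people rode little or not at all, or the pattern of use the row names

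*Protocol article*

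**What the plan says.** Table 2 of the protocol article lists, under the objective of estimating potential effects, the row "E-cycling behaviour: # journeys, distance travelled, pattern of e-bike use", measured during the intervention with the bike odometer and a cycling GPS unit. Its analysis entry is mean and SD, and nothing else.

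The Quantitative analysis section sends the reader to Table 2 for the analysis of each outcome, and leaves e-cycling during the intervention out of the change-score comparison. That section does offer a choice of summaries, but for a different subject: "Characteristics of the sample will be summarized using descriptive statistics (means and standard deviations, medians and interquartile ranges, or frequencies and percentages as appropriate". As worded, the choice covers sample characteristics and not the e-cycling row.

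The section on e-cycling during the intervention says that the pattern of use across the 12 weeks is to be determined from the GPS unit, and that the odometer gives total distance. Under E-bike loan, "no specific daily or weekly cycling frequency or distance targets will be imposed on participants by the researchers".

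**The concern.** The row names three things: journeys, distance and pattern of use. The first two are bounded at zero. Each person decides how much to ride, and some may ride very little or stop. With so few people, a mean can sit well away from what a typical participant did. The third, a pattern over 12 weeks, is not something that one mean and SD can express.

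What is at stake is how well the pilot describes uptake. A team designing the definitive trial will want to know how many people used the bike and whether they kept using it. Sessions attended and instructor contact describe delivery and attendance, and the accelerometer and personal GPS data cover one week. If this row is reported as written, no stated quantitative result gives the number who rode across the loan.

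**Working it through.** The plan gives no figure, SD or distribution for e-bike use, so there is nothing to reproduce. The check is whether mean and SD can carry the information that the row calls for.

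**Number of people.** "A total of 40 participants will be randomized in a 1:1 allocation ratio to the two study arms" (Study design), so 40 × 1/2 = 20 ride during the trial period. Allocation and randomization confirms the cap: "A maximum of 20 participants will be randomized to each of the trial arms". Under Sample size, "a retention rate of approximately 80% is anticipated", so about 20 × 0.80 = 16 may be retained. One person is 1/20 = 5% or 1/16 = 6.25% of the data.

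**Assumed distances.** All values below are assumptions, in km over 12 weeks. SD uses n − 1.

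| Assumed use | Mean | SD | SD/mean | Median | IQR | Non-users | Below mean |
|---|---|---|---|---|---|---|---|
| A: 4 at 0, 4 at 20, 8 at 150, 4 at 1000 | 264 | 383 | 1.45 | 150 | 20–150 | 4 | 16/20 |
| B: 6 at 0, 4 at 10, 7 at 100, 3 at 1200 | 217 | 426 | 1.96 | 55 | 0–100 | 6 | 17/20 |
| C: 4 at 0, 3 at 20, 6 at 150, 3 at 1000 (n = 16) | 248 | 379 | 1.53 | 150 | 15–150 | 4 | 13/16 |
| D: 5 at 0, 15 at 300 | 225 | 133 | 0.59 | 300 | 225–300 | 5 | 5/20 |
| E: gamma-shaped, scaled to the mean and SD of D; lowest value 41 | 225 | 133 | 0.59 | 200 | 130–292 | 0 | 11/20 |
| F: even spread from 200 to 290 | 245 | 30 | 0.12 | 245 | 220–270 | 0 | 10/20 |

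Arithmetic for D: mean = (5 × 0 + 15 × 300)/20 = 225; SD = √[(5 × 225² + 15 × 75²)/19] = √(337,500/19) = 133.

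- **Heavy riders (A, B).** The mean is 264/150 = 1.8 and 217/55 = 3.9 times the median, and 16 to 17 of 20 people lie below it.
- **Non-users (D against E).** The mean and SD are the same, but a quarter of the group never rode in D and nobody failed to ride in E. The SD is well below the mean in both, so nothing looks unusual. The IQR of D does not reach zero either, so a count of non-users is needed as well as quartiles.
- **Even use (F).** Mean and SD serve perfectly well.

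**Smooth skew among riders.** If use is log-normal with log-SD s, mean/median = exp(s²/2): 1.13, 1.32, 1.65 and 2.18 for s = 0.5, 0.75, 1.0 and 1.25. SD/mean = √(exp(s²) − 1), which is 1.31 at s = 1.0.

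**Pattern.** This needs no distributional assumption. Someone riding 25 km in each of 12 weeks (12 × 25 = 300) and someone riding 100 km in each of three weeks and then stopping (3 × 100 = 300) contribute identically to the mean and SD of total distance.

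**The case against.** The best case for leaving the row alone has four parts.

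- **It decides nothing.** The stated primary outcomes are recruitment, consent, retention, adherence to study procedures and data provision. None of the five progression criteria uses riding; the adherence criterion counts sessions. This stands, and it limits the point to a minor one. A reader might infer that a misleading mean could tip the decision on a definitive trial; the criteria as written give no route for that.
- **Other exposure measures exist.** A reader might take e-bike use to be the only measure of intervention dose. It is not. The Process evaluation section records sessions attended and instructor contact as intervention intensity, and the Behavioural outcomes section measures MVPA from e-cycling and mode of transport in the final week, alongside a travel diary. What remains true is narrower: this row is the only quantitative outcome covering riding over the whole loan.
- **The SD would give the skew away.** In A to C the SD is 1.45 to 1.96 times the mean, which for a non-negative quantity plainly signals skew. So it goes too far to say that a few enthusiasts could pass unnoticed as typical use. But the SD never supplies the number of low or zero users, and D shows that it need not look odd when a quarter never ride.
- **This is a condensed article.** Fuller displays may be in an analysis plan that is not shown, and the cell may be shorthand. That is fair for added detail. But the article does not stay silent: it names one summary for this row, and that summary cannot fit one of the three things listed.

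Leaving e-cycling out of the change scores is no weakness, since the row has no baseline measurement.

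**Conclusion.** The point holds as a minor one. Mean and SD are a stated choice for this row, not a gap. They cannot give the number of people who rode little or not at all, and they cannot describe use over 12 weeks. The second conclusion follows from the row itself. How much the first matters depends on the actual distribution, which the article does not give. Under the assumptions tried, the effect runs from none (even use) to a mean 3.9 times the median with 6 of 20 people not riding. The documents make skew and non-use plausible through free choice of use, a floor at zero and a small group, but do not establish either.

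**What to change.** Revise the e-cycling row of Table 2 as follows.

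- Keep mean and SD, and add median, IQR and range for journeys and distance.
- Give the number and percentage of participants allocated to the intervention with no e-bike use over the loan, checked against the odometer total.
- Give median distance and the number riding in each of weeks 1 to 12 among participants with GPS data, and report missing GPS data separately from non-use.

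The last separation matters. GPS records depend on the participant charging and using the unit and on Bluetooth or monthly manual upload, while the odometer gives only a total. An empty GPS record with distance on the odometer is missing data, not a non-user, and the odometer cannot confirm zero riding in any single week.

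The GPS and odometer data are already to be collected, so the cost is one table row and a little more analysis. The weekly figures will be only as complete as the GPS data.
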